#### Feedback survey

A user feedback survey was created by our group to evaluate participants’ experiences using the CR or control activities, and to evaluate participants’ beliefs about their study assignment to test the effectiveness of the blind. The first 13 items ask about tolerability, including enjoyment of the tasks, especially compared to other types of treatment, perception of difficulty, stressfulness of the activities, feelings of competency generated by participation, and whether users would continue to participate if given the option. Responses are given using a Likert scale (1–5) with higher scores indicating stronger response; 4 of the 13 items inquired about negative experiences such that higher scores were associated with more negative responses; these items were reverse scored so that in all cases a higher score indicates more positive response. Cumulative scores range from 13 to 65. Subjects were also asked in a forced-choice item to indicate which treatment condition they believed they were assigned to, and then asked to rate the certainty of their selection.

#### Additional outcome measures

We are also collecting neuroimaging data and measures of reward processing at baseline and post treatment in order to begin to examine baseline predictors of treatment response and mechanisms of action of the treatment. These procedures are offered in an “opt-in” format, meaning that participants do not have to consent to (or be eligible for) neuroimaging or reward processing tasks in order to participate in the CR trial.

### CR treatment

Given that this was the first extension of computer-based, drill and practice CR to patients with BDP, and the considerable overlap in terms of cognitive dysfunction in SZ and BDP, we selected a CR paradigm that has demonstrated efficacy in patients with SZ [24]. We selected a dose that – based on previous findings – was likely to be adequate to demonstrate cognitive effects, so that failure of the treatment would not likely be due to under-dosing. Active treatment involved 70 hours of computer-based activities at an intensity of three sessions per week using the BrainWorks programs by PositScience. Games were developed based on a recovery model of neural plasticity [53]. Many cognitive deficits (e.g., memory) are believed to be secondary to more core processing issues, including slow processing speed and poor encoding of sensory stimuli. Thus, these programs target root causes of abnormalities in brain function using a “bottom-up” approach, training sensory processing early in the program and adding “higher-order” tasks as the activities progress. Programs are designed to improve processing speed and efficiency (e.g., quick and accurate stimulus identification), reaction time, attention, concentration, and working memory. Programs self-adjust based on user performance to keep participants working at 80 % proficiency.

The CR paradigm is accessed online through a web portal created by BrainWorks, which allows study participants to engage with the program from any computer with Internet access. In order to reduce travel burden and allow greater flexibility for participants to complete the sessions they are allowed to complete two of the three weekly sessions remotely; one weekly session is to be completed with the study staff at the study site in order to provide coaching and bridging opportunities. Study administrators track participant adherence remotely through an administrator account, which allows staff to check when participants logged onto their programs and what they did while they were there.

### Computer control

We developed a computer-based control that mirrored the CR program in number of training sessions, online format, administrator contact, and general activity format so as to control for as many nonspecific effects of the CR treatment as possible. However, the control does not include tasks that should substantially address the cognitive deficits typical of BDP. Thus, the control condition involves engagement in active computer games, but without the step-wise, “bottom-up” approach or adaptive nature of the tasks. In order to monitor adherence to the protocol – a particular concern given the remote access to games offered in the CR condition – it was necessary to develop a comparison condition that also permitted study staff to track remote usage during at-home sessions. Sessions were created using generic games administered via the online interface Sporcle (www.Sporcle.com), a collection of thousands of quiz-type activities. We carefully selected several hundred games to include a broad array of activities that most people have knowledge of. Games included identification activities (e.g., identify pictured fruits and vegetables), content-based activities (e.g., label states on a map), and some timed activities (e.g., complete as many basic arithmetic problems as possible in 5 minutes). Data from thousands of users documenting accuracy rates for each quiz are freely available online; we used these data to rate each quiz for difficulty based on total quiz completion/accuracy rates. This was undertaken to ensure that games were not overly difficult. Games were excluded if they had an accuracy rate of less than 40 %. Average accuracy for selected quizzes was approximately 73 %.

Similar to the CR condition, an administrator account allows study staff to track subject activity via a social networking-style format that allows the administrator to request that participants allow themselves to be followed online. Through this process the study administrators are able to determine when participants logged in, which games they engaged in, and what their response accuracy was. In order to maintain confidentiality all subjects are assigned a study-based user identity (ID) that allows the administrator to identify individual participants without revealing any personal information.

Games were divided into 70 sessions of prescribed activities to mirror the format and length of the treatment condition. Types of activities were distributed so that no single session included only one type of game (e.g., all rapid-response games). Participants are given “prescription cards” each week listing the games they are to engage in during each weekly session. As in the CR condition, participants may elect to play two of the three weekly sessions remotely via web access; one weekly session is completed at the study site with staff.

### Procedures

Randomization was started using a simple randomization approach, but due to increasing imbalance this approach was switched to a blocked random design with a block size of 10. The Research Randomizer tool (www.Randomizer.org) was used to generate the random allocation sequence. The principal investigator (PI), [name], generated the sequence, which was given to enrollment staff who are responsible for group assignment. We employed a parallel design with an allocation ratio of 1:1. The randomization key is kept by a single staff member, who provides the treatment and/or communicates assignment information directly to treatment staff. Assessment staff are not informed of group assignment (see below). Participants are not informed of their group assignment. During the consent process participants are explicitly informed that participation in the study involves random assignment to either the treatment condition or an active control, that they may be assigned to the control condition, and that they will not be informed of their group assignment. Participants are informed that they may request knowledge of their study assignment at the end of the follow-up period.

In this study, both patients and assessment staff remain blind to group membership through completion of the follow-up assessment; however, treatment administrators are not able to remain blind to group assignment. Treatment administrators meet with participants weekly to discuss their progress and one session weekly is completed on site with treatment staff; thus, treatment administrators are not able to remain blinded to group. We attempt to maintain the participant and assessment staff blind in several ways: enrollment staff and treatment administrators never conduct assessments at any time point; the assessment staff are not located in the same office space as the treatment administrators, and do not observe or participate in weekly sessions; participants are reminded that assessment staff cannot know which group they were assigned to and it is requested that any mention of the activities be avoided during assessments; subject IDs and enrollment dates are not included in the database accessible to staff who are blind to group membership, and non-sequential dummy codes are created for the purposes of data access by blinded staff members. The feedback survey described above contains two questions regarding participants’ beliefs about group membership, which aim to assess which group participants believe they were in, and their certainty about this belief. These data are used to help us determine whether or not we were able to maintain the blind.

Both conditions involve 70 sessions (3 per week for 24 weeks). All participants attend one session per week at the study site; two sessions are completed remotely via Internet login. Weekly in-person sessions include an update (CR and control) and a bridging session (CR only), plus one CR or control session with study staff. Study staff are able to track user progress and adherence via an administrator account, and send reminder calls or emails upon request or if participants do not complete their at-home sessions in a timely fashion.

Assessments are conducted at baseline, midpoint (after approximately 25 hours of training) post treatment (within 1 week of completing the treatment/control), and at follow-up (6 months after completion of the treatment/control). All subjects complete clinical and cognitive assessments; neuroimaging is presented as an “opt in” portion of the study. Clinical and cognitive assessments are typically conducted in the same session. Baseline assessments occur 2 weeks or less prior to the start of training; post-treatment assessments are conducted within 1 week of completing the final training session.

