### Limitations

While extensive efforts will be made to minimize missing data, attrition is a major concern in long-duration CR paradigms. We have implemented several techniques for minimizing attrition including monetary bonuses for reaching session milestones (awarded after 10 sessions, 30 sessions, and 50 sessions, in increasing amounts), regular phone and email contact from study staff reminding subjects to complete sessions at home, weekly in-person visits, and weekly session tracking feedback that displays progress and time to next bonus graphically. However, attrition remains a concern. Thus, for all analyses we will use statistical methods that incorporate partially observed data, and assess the sensitivity of results to different assumptions about the mechanism by which data are missing.

In any clinical trial the potential for bias in recruitment or allocation is a concern. All potential subjects meeting enrollment criteria are offered the opportunity to participate; special efforts will be made to ensure that the enrollment of women and minorities matches the demographics of the region. Allocation is done using a blocked random design based on number sequence, without consideration of participant characteristics. Thus, the main source of bias in this study is likely in non-random characteristics of participants who do or do not adhere to the study procedures. As noted above, we will use statistical methods to minimize the potential for such post-randomization bias.

In terms of masking, we have developed an approach that maximizes our ability to include blinding of participants and study staff; however, as noted above, while assessment staff are able to remain blinded to study assignment, due to the nature of the intervention treatment staff are not. Thus, there is the potential for information about group membership to inadvertently become known to participants or to assessment staff. Because poor masking of treatment allocation is associated with potential inflation of treatment effects [21], the issue of blinding in treatment studies is of key importance. Our post-treatment feedback survey suggests that we have been able to maintain participant blinding, but the potential for a break in the blind remains a limitation.

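### The allocation sequence is given to the staff who enroll and assign, so upcoming assignments can be foreseen and selection bias is possible

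*Protocol article*

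**What the plan says.** All of this is in the protocol article.

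- **Who holds the sequence (Procedures).** The principal investigator "generated the sequence, which was given to enrollment staff who are responsible for group assignment".
- **Who holds the key (Procedures).** A little later: "The randomization key is kept by a single staff member, who provides the treatment and/or communicates assignment information directly to treatment staff".
- **How the sequence was built (Procedures).** Randomization began as simple. Then, "due to increasing imbalance this approach was switched to a blocked random design with a block size of 10". The ratio is 1:1.
- **What is protected (Procedures).** Participants and assessors stay blind, treatment administrators do not, and "enrollment staff and treatment administrators never conduct assessments at any time point".
- **How allocation bias is discussed (Limitations).** The section raises bias in recruitment or allocation and says that everyone who meets the criteria is offered entry. It adds: "Allocation is done using a blocked random design based on number sequence, without consideration of participant characteristics". It then places the main source of bias in adherence.
- **Analysis (Statistical approach).** The primary mixed model adjusts for baseline cognition.

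No device is described that hides an assignment until a participant is committed to the trial.

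**The concern.** Concealment and blinding are separate safeguards. Blinding protects what happens after assignment. Concealment keeps the next assignment unknown until the decision to enter a participant is final. Here the article states as procedure that the sequence goes to the staff who enroll and assign. This is not a detail left to a fuller document.

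A person who can foresee the next arm can, without intending to, bring a motivated candidate forward, delay another, or press harder for consent in one case than in the next. The arms then differ in prognosis at entry. Motivation and readiness matter in a programme of 70 sessions over 24 weeks, and baseline MCCB measures them poorly, if at all.

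The sentence about a single key holder does not settle the matter. It is hard to square with a sequence given to enrollment staff, and the custodian it describes may also deliver treatment.

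**Working it through.** **Inputs from the article.** Power calculation: 100 participants, about 50 per group, attrition about 15%, one-tailed alpha 0.05, 80% power for an effect of 0.54. Procedures: ratio 1:1, block size 10. Trial status: 76 enrolled by July 2015.

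**Input assumed.** η is the shift in prognosis, in SD, that staff produce according to the arm they expect: up for CR, down for control. The article gives no such figure. The range shown is 0.05 to 0.20.

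**1. The plan's own figure.** Completers per arm: 50 × 0.85 = 42.5. Standard error of the difference: √(2/42.5) = 0.2169 SD. Power: Φ(0.54/0.2169 − 1.645) = Φ(0.844) = 80.1%. The stated 80% is reproduced, so 0.2169 is a fair yardstick for what follows.

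**2. How much can be foreseen.** Let p be the proportion of assignments predicted correctly.

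- With the list: p = 1.
- Simple randomization without the list: p = 0.5.
- Fixed blocks of 2m = 10 without the list, with block size, block boundaries and past assignments known: expected correct guesses per block are m + (2^(2m)/C(2m,m) − 1)/2 = 5 + (1024/252 − 1)/2 = 6.53. So p = 65.3%.
- In the same setting, assignments at the end of a block that are certain: 2m/(m+1) = 10/6 = 1.67 per block, or 16.7%.

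**3. What that could do to the comparison.** The mean prognosis is +η(2p − 1) in CR and −η(2p − 1) in control, so bias = 2η(2p − 1). The one-sided error rate is 1 − Φ(1.645 − bias/0.2169).

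| η (assumed) | Bias, list known | Error rate | Bias, guessing in blocks of 10 | Error rate |
|---|---|---|---|---|
| 0.05 | 0.10 SD | 11.8% | 0.03 SD | 6.6% |
| 0.10 | 0.20 SD | 23.5% | 0.06 SD | 8.7% |
| 0.20 | 0.40 SD | 57.9% | 0.12 SD | 14.0% |

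At η = 0.10 with the list known, the bias is 0.20/0.54 = 37% of the planned effect. These figures use the simple two-group comparison behind the power calculation, not the joint test of group and group-by-time. They make no baseline adjustment, so they are too high for any shift that shows in baseline MCCB.

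**4. Whom a change can still protect.** 100 − 76 = 24 participants, fewer if enrollment has continued since July 2015.

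**The case against.** The strongest reply is that the article limits the routes by which foreknowledge could act. Enrollment staff carry out no assessments. If the PANSS and YMRS ratings used for eligibility are made by assessment staff (the article does not say), bending a symptom threshold to suit an arm is unlikely. All eligible patients are said to be offered entry, which bears on selective offering. The key holder is not said to recruit. These points stand, and they narrow the mechanism to timing and encouragement. They do not restore concealment, because an offer to everyone fixes neither when it is made nor how warmly.

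The block size also matters less than it first seems. While the list is in hand it adds nothing. The 65% figure applies only once the list is withdrawn, and needs someone who knows the block boundaries and every earlier assignment. The article does not say that recruiters without the list know these. Block size therefore belongs in the remedy and is not a separate fault.

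A reader might go further in three ways that the article does not support:

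- **That the model is wrong without a term for the simple and blocked phases.** The ratio is 1:1, the stated reason for the switch was imbalance and not outcomes, and such a covariate is ordinary content for an analysis plan that is not shown. The article gives no split or date for the first phase from which to size an effect.
- **That Limitations misdescribes the trial as blocked throughout.** Its present-tense wording fits the procedure then in force, and Procedures discloses the earlier phase openly.
- **That comparing results before and after concealment would reveal the bias.** With about 38 per arm before and 12 after, the standard error of the difference in effects is √(2/12 + 2/38) = 0.47 SD before attrition. A bias of 0.20 SD would not be seen.

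**Conclusion.** The point holds on the stated procedure: those who enroll can foresee assignments, and who else holds the list is unclear. The article shows that selection bias was possible, not that it happened, and it does not establish that every recruiter saw every assignment.

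The block arithmetic is exact under its conditions. The biases in SD follow from the assumed shift and should be read as a scale: 0.10 to 0.40 SD with the list and 0.03 to 0.12 SD by guessing, for shifts of 0.05 to 0.20 SD. Blinded assessment does not act on this bias, and baseline MCCB adjustment removes only part of it. Limitations names adherence as the main source of bias without saying that enrollment staff held the sequence. On what Procedures states, allocation belongs beside it.

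**What to change.** 1. **Reconcile the two statements in Procedures.** Say who received the sequence, who keeps the key, and whether any of them recruits or treats.
2. **Conceal the remaining assignments.** Withdraw the list from enrollment and treatment staff. Use a computer allocation that releases each assignment only after consent, eligibility and baseline assessment are logged. The existing list may already have been seen, so generate the rest afresh, by someone who neither enrolls nor treats.
3. **Vary the block sizes and do not disclose them.** Otherwise the guessing route stays open once the list is gone.
4. **Report the exposure for those already enrolled.** State that enrollment staff held the sequence, and in Limitations name allocation as a possible source of bias alongside adherence.

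The cost is a small procedural amendment and some set-up, with no change to the sample size or the 80% power. Its limit is that it protects only participants not yet enrolled, about 24 of 100 at July 2015. For the other 76, disclosure is what remains.

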**Methods/Design:**

The Treatment to Enhance Cognition in Bipolar Disorder study is an investigator-initiated, parallel group, randomized, blinded clinical trial of an Internet-based cognitive remediation protocol for patients with bipolar disorder I with psychosis (*n* = 100). We also describe the development of our dose-matched active control paradigm. Both conditions involve 70 sessions of computer-based activities over 24 weeks. The control intervention was developed to mirror the treatment condition in dose and format but without the neuroplasticity-based task design and structure. All participants undergo neuropsychological and clinical assessment at baseline, after approximately 25 hours of study activities, post treatment, and after 6 months of no study contact to assess durability. Neuroimaging at baseline and post treatment are offered in an “opt-in” format. The primary outcomes are scores on the MATRICS battery; secondary and exploratory outcomes include measures of clinical symptoms, community functioning, and neuroimaging changes. Associations between change in cognitive measures and change in community functioning will be assessed. Baseline predictors of treatment response will be examined.

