### Challenges in cognitive remediation

Typical CR paradigms require multiple training sessions weekly, which may be prohibitive for potential study participants. Many of the CR programs that have shown efficacy in patients with SZ have studied chronic patients who are able to attend sessions at community-based programs multiple times per week, due to high levels of disability and low instrumental role involvement (e.g., [24]). While patients with BD exhibit considerable disability, especially compared to premorbid functioning, patients with SZ or schizoaffective disorder (SZA) exhibit greater morbidity and disability on average [25], indicating that treatments requiring multiple weekly sessions at study sites may be unrealistic, especially for patients who are even partially engaged in work or school roles. With rapid advancements in online cognitive training programs, there is considerable potential for Internet-based treatments to improve access to training for patients. However, reports suggest that face-to-face “bridging” sessions, which create an opportunity for subjects to explicitly consider implementation of newly-developed cognitive skills in daily life, are important for generalizing the effect of CR treatments to daily functioning [26]. Thus, a tension exists between reducing participant burden through remote access and conducting treatment delivery in the most effective manner.

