## Discussion

The present study is the first we are aware of to implement an Internet-based CR paradigm in patients with BDP and to develop a comparable Internet-based control. The hybrid online/study site format allows accessible treatment while providing opportunities for staff contact and bridging. Our newly developed web-based control is comparable to the treatment in terms of administration and interface: it is dose-matched, including requirements for in-person visits and study staff contact; administrator oversight permits adherence monitoring; sessions are similar in format to those of the CR paradigm.

Based on preliminary feedback from our feedback survey, participant blindness can be successfully maintained with our present paradigm. Responses from the first 22 participants to complete the survey showed that subjects did not differ in terms of which condition they believed they were randomized to: 86 % of subjects in the treatment and 63 % of subjects in the control reported believing that they had participated in the active CR treatment (Chi^2^ = 1.56, *p* = 0.20). On a three-point scale evaluating confidence in their belief of their reported assignment (very (3), somewhat (2), or not at all (1)), participants had low confidence in their ratings in both treatment and control conditions (mean = 1.64, SD = 0.63 and mean = 1.63, SD = 0.92, respectively; *t =* 0.05, *p* = 0.96). Our newly developed active control permits examination of specific elements of our CR paradigm by accounting for many of the nonspecific elements of participation in the study while maintaining the participant and assessment staff blind.

Ultimately, our primary aim is to evaluate efficacy of this CR program compared to active control. We also aim to examine predictors of treatment adherence and response, and neurobiological mechanisms of action using magnetic resonance imaging (MRI) techniques. Better understanding of both predictors of treatment response and the mechanisms of action of CR will allow further refinement and individualization of treatment efforts. We will also be able to examine the role of baseline characteristics, reward processing, and neurobiological response in the relationship between cognitive and functional outcomes.

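### Weekly bridging is given to the CR arm only, so the control is not matched on staff contact as claimed, and effects on functioning cannot be credited to the computer training alone

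*Protocol article*

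**What the plan says.** The Procedures section describes the weekly on-site visit: "Weekly in-person sessions include an update (CR and control) and a bridging session (CR only". Both arms also complete one session with staff at that visit. The CR treatment section gives the visit's purpose in that arm: "one weekly session is to be completed with the study staff at the study site in order to provide coaching and bridging opportunities". The Computer control section describes an on-site session with staff and mentions no bridging.

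Three places describe the control as matched:

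- Computer control: it "mirrored the CR program in number of training sessions, online format, administrator contact, and general activity format".
- Discussion: "it is dose-matched, including requirements for in-person visits and study staff contact".
- Abstract, Methods/Design: it was built to "mirror the treatment condition in dose and format but without the neuroplasticity-based task design and structure".

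The Discussion adds that the control "permits examination of specific elements of our CR paradigm by accounting for many of the nonspecific elements of participation in the study". On bridging itself, the Background (Challenges in cognitive remediation) cites reports that such face-to-face sessions "are important for generalizing the effect of CR treatments to daily functioning". The Limitations section does not mention that only one arm receives them.

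**The concern.** The matching statements tell the reader that the arms differ in the design of the computer tasks and that contact with staff is held equal. The Procedures section shows a second difference: a recurring face-to-face component delivered by staff to one arm. It is also the component that the article regards as important for carrying gains over into daily life.

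What is at stake is attribution. Community functioning is measured by the MCAS and SOFAS, and the secondary aim asks whether cognitive change mediates change in functioning. If CR does better on functioning, the design cannot say whether the training, the bridging or the two together produced the difference. A report relying on the matching statements would credit the training.

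**Working it through.** **1. Compare the arms, component by component** (Procedures, CR treatment, Computer control).

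| Component | CR | Control | Matched? |
|---|---|---|---|
| Sessions | 70 over 24 weeks | 70 over 24 weeks | yes |
| On-site visits | one per week | one per week | yes |
| Online format, remote tracking | yes | yes | yes |
| Weekly update | yes | yes | yes |
| On-site session with staff | yes | yes | yes |
| Bridging session | yes | no | **no** |
| Minutes of staff contact | not given | not given | cannot be shown |

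The matching claim holds for counts and format. It fails for the content of contact. Equal duration would require the control visit to be lengthened to compensate, and nothing in the article says that it is.

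**2. Size in sessions.** One visit a week for 24 weeks gives up to 24 bridging sessions in CR and 0 in control.

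**3. Size in hours (assumption).** The article gives no length for bridging. At an assumed 10 to 30 minutes per visit with no compensating time in control, the excess is 24 × 10 / 60 = 4 hours to 24 × 30 / 60 = 12 hours per CR participant who attends every visit.

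**4. What this could do to a functional comparison (illustration).** First, the plan's own power figure, to fix the sample size. With 100 randomized and 15 % attrition, 100 × 0.85 = 85 are analysed, or 42.5 per arm. With power = Φ(d√(n/2) − z), d = 0.54 and one-sided alpha 0.05:

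0.54 × √(42.5/2) − 1.645 = 2.489 − 1.645 = 0.844, and Φ(0.844) = 80.1 %.

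The stated 80 % is reproduced. Now suppose training has no effect on functioning and bridging alone shifts it by d. The article gives no such effect, so a range is shown. The last two columns give the chance of a significant difference favouring CR in a simple two-group comparison.

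| Assumed bridging effect d | One-sided 0.05 | Two-sided 0.05 |
|---|---|---|
| 0.1 | 12 % | 7 % |
| 0.2 | 24 % | 15 % |
| 0.3 | 40 % | 28 % |
| 0.4 | 58 % | 45 % |

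These are not false-positive rates for the package, because a bridging effect is a real effect of the package. They show how often a difference would appear that the training did not cause.

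**5. The mediation model.** The Statistical approach section models functioning on treatment group, adjusted for cognitive (or clinical) change. Any bridging effect on functioning that does not pass through measured cognition falls into the remaining group term, together with any direct effect of training. Bridging goes to all of one arm by design and to none of the other, so the group comparison cannot separate the two.

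**The case against.** The strongest reply is that the article never promises to isolate the computer training. The Discussion says that many, not all, nonspecific elements are accounted for. The CR treatment section openly includes bridging in the CR package, and the primary aim is the efficacy of that program against the control. This stands: the package contrast is randomized and valid. It does not rescue the specific statements that staff and administrator contact are matched, nor the attribution of functional results.

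A reader might infer several stronger things that the documents do not support:

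- *The primary comparison is confounded.* Bridging is a bundled part of one arm, not a baseline imbalance. The article links bridging to daily functioning and says nothing of an effect on the MCCB composite.
- *Staff time is known to be unequal.* It is likely, but no visit lengths are given. A journal article may leave these to the full protocol, so their absence is not a fault.
- *The mediation analysis is invalid.* A path that bypasses cognition appears in the remaining group term, which the model keeps. It restricts how that term may be read and does not by itself void the indirect effect.
- *The blind is broken.* Skill-focused discussion in one arm could be a cue, but this is speculative. Among the first 22 survey respondents, 86 % in CR and 63 % in control believed they had the active treatment (p = 0.20), with mean confidence of 1.64 and 1.63. That is too few to settle the matter either way. Assessors do not take part in the weekly sessions, and the Limitations already name a possible break in the blind.

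**Conclusion.** The point holds in a limited form. The article claims matching on staff contact that its own procedures do not provide, and the Limitations do not disclose this. The documented difference is up to 24 bridging sessions in one arm only. Any difference in hours, and any effect of bridging on functioning, rests on the assumptions shown above.

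The consequence is confined to interpretation. Effects belong to training plus bridging, and the restriction matters most for the MCAS, the SOFAS and the mediation aim. The primary MCCB analysis, the sample size and the randomized comparison of the package need no change. The point is moderate in weight: the text is wrong as written and should be corrected, but it does not threaten the primary result.

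**What to change.** Reconcile the sections as follows:

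1. Define the tested contrast as CR plus bridging versus the computer-game control.
2. In the Abstract, Computer control and Discussion, limit the matching claim to the number of sessions, the number of in-person visits and the online format. Drop or qualify the wording on staff and administrator contact, and say in the Abstract that bridging is withheld from control as well as the task design.
3. Withdraw or qualify the statement that the control permits examination of specific elements of CR.
4. Add to the Limitations that functional differences cannot be assigned to the training alone, and that a group effect remaining in the mediation model may reflect bridging.
5. Where feasible, report staff-contact time by arm. Records started now would be incomplete for earlier participants, and the report should say so.

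Items 1 to 4 cost only rewording; item 5 costs a small data field. The control condition should not be altered mid-trial. With 76 of 100 enrolled by July 2015, 100 − 76 = 24 participants remained to be enrolled, and a change would create two control conditions for little gain.
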